**ABSTRACT:**

Glaucoma is the leading cause of irreversible blindness in the United States and can dramatically affect the quality of life for patients with moderate to severe visual loss. Glaucoma is characterized by a specific pattern of optic neuropathy and visual field loss secondary to death of retinal ganglion cells and represents the final common pathway of multiple diseases which affect the eye. Elevated intraocular pressure (IOP) is the most common known risk factor for glaucomatous damage and at the current time, the only modifiable risk factor for which treatment has been proven to have an effect on preventing or slowing the progress of the disease.

IOP increases on assuming a body position other than the upright one. (21,12,13,7,4) A small variation can be detected when moving from the sitting to recumbent position.(2,22) The increase in IOP is directly related to the inclination of the body toward the complete inverted position.(5) IOP begins to rise upon assuming a head down position and with the body vertical, results in doubling of the IOP,(23) which remains elevated as long as this position is maintained.(8,14)

Postural yoga (asanas), including headstand posture (sirsasana), is, along with breathing exercises (pranayama) and meditation (dhyana), one of the three basic components of hatha yoga. Yoga has become a popular practice in the western world. In 1998 an estimated 15 million American adults had performed yoga at least once in their lifetime.(3) Recent studies have described an elevation in IOP following sirsasana (headstand) posture, particularly in glaucoma patients.(3,9) In the sirsasana position there was a uniform 2-fold increase in IOP.(3,9,15)

Those who have been practicing yoga for many years may present with glaucomatous optic atrophy and visual field defects despite a normal IOP when measured in the sitting position. This may lead to diagnosis of normal tension glaucoma. The term “intermittent glaucoma” was suggested by Schuman et al in their investigation of high resistance wind instrument players, (19) and may be also used for those who practice inverted positions during yoga and otherwise exhibit normal intraocular pressures at office visits.

Previous studies evaluating IOP and body position have typically used a fixed measurement sequence. This presents difficulties in interpretation because IOP measurements are affected by the measurement sequence,(16) and repeated measurements of IOP can result in a decrease in the readings.(1, 10) As a result, the magnitude of the changes owing to body position have been uncertain, with different studies reporting differences between sitting and supine IOP ranging from 0.3 to 5.6 mmHg for normal and glaucoma subjects (23,11,20).

We plan to use standard ophthalmic tonometry devices to monitor IOP changes during different standard yoga asanas. An example of a standard yoga asana is the adho mukha svanasana, which is most commonly known as the downward facing dog pose. This asana is performed by kneeling on all fours with hands beneath the shoulders and the knees directly beneath the hips. The hips should be hip width apart and the fingers spread wide apart. Tuck the toes under as inhaling and lifting the body up, keeping the shoulders back and pushing backward on the hips, keeping the heels down as much as possible. Exhale and relax the neck muscles while lowering the head to look back at the feet.(17) This is shown in Figure 1.

[figure not shown]

Figure 1. Adho Mukha Svanasana.(17)

Another example of a common asana is the uttanasana, which is most commonly known as the standard forward bend pose. This asana is performed by resting the hands on the hips, exhaling and bending forward from the hip joints. By keeping the knees straight, place the fingertips or palms on the floor beside the feet or touching the back of the ankles with the palms (this is shown in Figure 2). This can also be modified by crossing the forearms and holding the elbows (this is shown in Figure 3). Allow the head to hang loose and release all the tension in the back and shoulder blades.(17)

[figure not shown]

Figure 2. Uttanasana with palms on the floor.(17)

[figure not shown]

Figure 3. Uttanasana modified.(17)

Through the asana change analysis we aim to further our understanding of the differentiation of IOP during standard yoga asanas of glaucoma and healthy participants. To the best of our knowledge, there have been no studies on the IOP variation with asanas, other than Sirsasana.

**DISCUSSION:**

**A) Specific Aims**

We plan to identify the IOP difference between normal and glaucomatous eyes using standard ophthalmic tonometry devices while subjects are performing standard yoga asanas. The IOP of participants will be measured prior, immediately at start of the asana, 5 minutes into the asana, and immediately after assuming a sitting position. The patient will wait 10 minutes and a final IOP will be taken.

**Study Design**

Participants will be identified and recruited from 1) patients at Glaucoma Associates of New York who are under the care of Drs. [name], [name], [name], and [name]; 2) through yoga centers in New York; and through yoga instructors who are patients of the practice. A total of 20 patients will be tested – 10 glaucoma patients and 10 control patients.

Technical and medical staff, under the supervision of [name], will aid participants in the completion of standard yoga asanas.

Data will be de-identified. De-identified data may be retained by the Investigators for analyzing purposes. The clinical coordinator of the project will oversee involvement of other staff for the procedures.

**Study Procedures**

Ophthalmologists will:

1. Identify subjects
2. Demographics, medical and ophthalmic history, glaucoma family history and ocular findings will be recorded for each study participant.
3. Obtain informed consent.
4. Collection of data will be obtained at Glaucoma Associates of New York.
5. Participants will have undergone a full eye examination; including refraction, slit-lamp examination, gonioscopy, visual fields, and optic disc exam prior to entry into the study.
6. The selected Yoga asana, for example adho mukha svanasana (Figure 1) or uttanasana (Figure 2) to name two, will be held for 5 minutes. Measurements of IOP will be collected using standard ophthalmic tonometry devices at set time points.
7. IOP taken OU prior to asana with tonometry.
8. Participant begins asana. A second IOP measurement is taken immediately after assuming the asana.
9. Five minutes after assuming the asana, a third IOP measurement is taken. Participant can then resume normal seated position.
10. Immediately assuming seated position, a fourth IOP measurement is taken.
11. 10 minutes after seated position, a final IOP is taken.
12. The study procedures will then be repeated in a different standard yoga asana.
13. De-identify and code data. All data files will be de-identified, with the patient's identifiers removed from the sample and a unique code assigned.

**B) NATURE OF CONTACT WITH HUMAN SUBJECTS**

1. Level of Risk for patients

__x__ _Minimal Risk

______ Minor Increase over Minimal Risk

______ More than Minor Increase over Minimal Risk

1. Potential Risks Include: A rise in IOP is expected but will be transient and not expected to be harmful.
2. Procedures to Minimize Risk: Routine Precautions

**C) SUBJECT ENROLLMENT**

Volunteers will be recruited from the patients at private offices of ophthalmologists. Persons between ages 18 – 80 will be entered. All participants must be familiar with standard yoga asanas. Participation is open to all who meet the diagnosis and age requirements.

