**Inclusion Criteria**

1. Written informed consent.
2. Age 18 to 80 years
3. Glaucoma patients or healthy controls with normal examination.
4. Yoga practitioner, someone who has been performing yoga practice for more than 12 months. Participant must also be able to maintain standard yoga asanas for a minimum of five minutes.

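### The 10 versus 10 glaucoma–control comparison has no age balancing across 18 to 80 years, and the protocol gives two conflicting recruitment sources without saying where controls come from

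*Protocol*

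**What the plan says.** The Specific Aims state one between-group objective: "We plan to identify the IOP difference between normal and glaucomatous eyes". Study Design sets the groups at "10 glaucoma patients and 10 control patients". Group membership is disease status, so there is no randomisation.

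The Inclusion Criteria give the same age window to both groups, "Age 18 to 80 years", and Subject Enrollment adds: "Participation is open to all who meet the diagnosis and age requirements". The document contains no matching, stratification or quota on age or yoga experience.

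Two sections describe recruitment:

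- Study Design starts with the specialist practice ("Participants will be identified and recruited from 1) patients at Glaucoma Associates of New York") and goes on to recruitment "through yoga centers in New York; and through yoga instructors who are patients of the practice".
- Subject Enrollment gives a single type of source: "Volunteers will be recruited from the patients at private offices of ophthalmologists".

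Both groups must have practised yoga for more than 12 months and be able to hold an asana for five minutes (Inclusion Criteria, item 4; Exclusion Criteria, item 2). Study Procedures, step 2, records demographics and medical and ophthalmic history. It does not name years of yoga practice.

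**The concern.** In an unrandomised comparison, the groups are comparable only as far as recruitment makes them so. Here the age window is 62 years wide, entry is open within it, and the origin of the controls is not stated. If the groups end up with different age or experience profiles, and these affect IOP in the pose, a difference read as an effect of glaucoma could partly reflect them.

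The Protocol offers a plausible route. Its Abstract says that the IOP rise is directly related to body inclination. It also allows the form of a pose to vary: uttanasana is described with the palms on the floor or with the forearms crossed, and the two asanas in Study Procedures are only examples. Anything that changes how a pose is held could therefore change the reading.

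This belongs in the protocol because it concerns who is enrolled. A statistical analysis plan can adjust for age once it is recorded, but it cannot make the groups comparable after enrolment or recover years of practice that were not collected.

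**Working it through.** **1. Recruitment passages side by side.** Study Design names practice patients, yoga centers, and yoga instructors who are practice patients. Subject Enrollment names only patients of ophthalmologists' offices. A volunteer from a yoga center who is not such a patient fits the first description and not the second. Neither section ties a source to glaucoma patients or to controls. This inconsistency needs no assumption.

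**2. Chance imbalance in age.** Inputs from the Protocol: ages 18 to 80, 10 per group. Assumption: ages are uniform over the window in both groups.

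- SD of age = (80 − 18)/√12 = 62/√12 = 17.9 years
- SE of the difference in mean age = 17.9 × √(2/10) = 8.0 years
- 95% range = ±1.96 × 8.0 = ±15.7, about ±16 years

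This is random imbalance, not systematic bias. It shows how little the design itself does to keep the groups alike in age. A narrower actual age distribution would shrink it in proportion.

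**3. Effect of a systematic age gap on the unadjusted comparison.** Let d be the gap between group mean ages in within-group SDs, and r the within-group correlation of age with the outcome. The bias is r × d outcome SDs. For a two-sided 5% t-test with 18 degrees of freedom, the noncentrality is r × d/√(2/10). The Protocol gives neither r nor d. With no true group difference, the false-positive rate is:

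| r | d = 0 | d = 1 | d = 2 |
|---|---|---|---|
| 0 | 5% | 5% | 5% |
| 0.1 | 5% | 5.5% | 7.1% |
| 0.3 | 5% | 9.7% | 24.6% |
| 0.5 | 5% | 18.5% | 56.2% |

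The result runs from no effect to a serious one, depending on two unknowns.

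**4. Cost of adjusting for age instead.** The variance of the age-adjusted group contrast is inflated by 1 + d²/4: 1.06 at d = 0.5, 1.25 at d = 1 and 2.0 at d = 2. As an illustration, an assumed gap of 20 to 25 years with SD 17.9 gives d = 1.1 to 1.4. The variance inflation is then about 1.3 to 1.5, and the SE is about 15% to 22% larger.

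**5. Room for that loss.** The Protocol states no power, alpha, SD or effect size, so its total of 20 cannot be reproduced. At two-sided 5% and 80% power (assumed), 10 per group detect a difference of 1.32 SD by t-test (1.25 SD by the normal approximation). There is little precision to spare.

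**The case against.** Several points on the other side stand.

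- **Sources by group.** A reader might infer that glaucoma patients will come from the specialist practice and controls from yoga centers, with an age gap to match. The Protocol does not say so. Its Study Design list is undivided, one of its categories is yoga instructors who are themselves practice patients, and Subject Enrollment gives one type of source for everyone. It gives no age or skill profile for any source.
- **Shared restrictions.** The requirements of more than 12 months' practice, a five-minute hold and familiarity with standard asanas apply to both groups. They limit differences in ability, though years and intensity of practice beyond them remain open.
- **Size in mmHg.** An assumed 20-to-25-year gap and an assumed slope of 0.05 to 0.10 mmHg per year give 20 × 0.05 = 1.0 to 25 × 0.10 = 2.5 mmHg. Neither input is in the Protocol, and a zero slope gives zero. The Abstract ties IOP to body inclination and says nothing about age.
- **Adjustment.** Demographics are recorded, and an analysis plan not shown may adjust for age. At the gaps considered above this costs precision but is feasible.
- **Within-person purpose.** The Protocol also wants to describe IOP change in asanas other than the headstand. Group imbalance does not bias each participant's own change.

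None of this supplies a balancing rule, states where controls come from, or resolves the conflict between the two recruitment sections.

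**Conclusion.** The point holds as a weakness of the between-group aim. The Protocol plans an unrandomised 10 versus 10 comparison over ages 18 to 80 with no age balancing, and its two accounts of recruitment disagree. The group difference is open to confounding by age and by yoga experience beyond the shared entry criteria.

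The stronger statement, that the contrast is confounded, is not supported: nothing in the document shows that the groups will differ in age or that age drives the IOP response. The magnitude is unknown. The ±16 years is chance variation under assumed uniform ages, and the false-positive rates depend on assumed correlations and gaps, returning to 5% when either is zero. This is a low-cost improvement to the design; it does not invalidate the study.

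**What to change.** 1. Reconcile Study Design and Subject Enrollment into one recruitment source list that applies to both groups, so that the origin of controls is clear.
2. In Subject Enrollment, state that controls will be frequency-matched to the glaucoma group on broad age bands fixed before enrolment. This removes most of a systematic age gap; differences within a band remain and can be adjusted for at small cost.
3. In Study Procedures, step 2, add years of yoga practice to the recorded data, so that the group comparison can be described by, or adjusted for, experience.

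The cost is somewhat slower control recruitment, since a control whose age band is already full would be turned away, and edits to these three sections. No extra participants, staff or procedures are needed.

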**Inclusion Criteria**

1. Written informed consent.
2. Age 18 to 80 years
3. Glaucoma patients or healthy controls with normal examination.
4. Yoga practitioner, someone who has been performing yoga practice for more than 12 months. Participant must also be able to maintain standard yoga asanas for a minimum of five minutes.

**Exclusion Criteria**

1. Unwilling to sign informed consent.

2. Participant cannot maintain standard yoga asanas for a minimum of five minutes.

3. Healthy subject does not have a normal ophthalmic examination.

Participants will not be reimbursed for participation in the study.

**Confidentiality**

[name] group will maintain a code protecting patient confidentiality.

**Duration of project and total amount of time required of each subject.**

Subject involvement is limited to the time of recruitment and completion of standard yoga asanas and IOP measurements. Recruitment (including patient education, questions, reading of the Informed Consent Form) is expected to take approximately 20 minutes. The time involvement for patients to complete the asanas and have their IOP taken will be about an hour of their time.

**D) SAFETY:** Medical staff and personnel will be with the participants during the

length of study time. All asanas will be performed by yoga practitioners. Risk of psychosocial harm to any kindred or group is none.

**E) RADIATION:** Not applicable

**F) DEBRIEFING:** Results from research will be de-identified and will only be used for research purposes. Any reference to the data from this point on for research purposes, including publication, is made by study identification number only. If, in the future, more concrete information about participant’s diagnosis becomes available from this study, the patient’s ophthalmologist will inform the patient.

**G) RISK/DECEPTION:** Physical, psychological, social, legal, economic, or any other risk. The anticipated risks associated with this study are those associated with the yoga asana.

**Justify conduction of "non-beneficial research"** (i.e.research involving investigation of a person, his/her body, life, or surroundings, which has no benefit to that person.)

The purpose of completing this asana is beneficial to all glaucoma and healthy patients who practice yoga. Studies have only been performed on headstand posture; a head down posture may also cause a significant rise in IOP. The testing of standard yoga asanas will help show the change in IOP in the asana. The practice of yoga could be dangerous for all yoga practitioners, especially glaucoma patients due to the change in IOP.

**H) CONFIDENTIALITY OF SUBJECTS:** The data of this research and summaries of medical histories may be used in publications, presentations, and grant or funding applications. No personal identifiers will be disclosed. In the unlikely event that an outside agency requests access to the data, the data would only be made available via requests approved by New York Eye and Ear Infirmary IRB.

[name] group will maintain possession of the signed Informed Consent Forms.

